## Abstract

**Background:**

Currently, main treatment strategies for early-stage non-small cell lung cancer (ES-NSCLC) disease are surgery or stereotactic body radiation therapy (SBRT), with successful local control rates for both approaches. However, regional and distant failure remain critical in SBRT, and it is paramount to identify predictive factors of response to identify high-risk patients who may benefit from more aggressive approaches. The main endpoint of the MONDRIAN trial is to identify multi-omic biomarkers of SBRT response integrating information from the individual fields of radiomics, genomics and proteomics.

**Methods:**

MONDRIAN is a prospective observational explorative cohort clinical study, with a data-driven, bottom-up approach. It is expected to enroll 100 ES-NSCLC SBRT candidates treated at an Italian tertiary cancer center with well-recognized expertise in SBRT and thoracic surgery. To identify predictors specific to SBRT, MONDRIAN will include data from 200 patients treated with surgery, in a 1:2 ratio, with comparable clinical characteristics. The project will have an overall expected duration of 60 months, and will be structured into five main tasks: (i) Clinical Study; (ii) Imaging/ Radiomic Study, (iii) Gene Expression Study, (iv) Proteomic Study, (v) Integrative Model Building.

**Discussion:**

Thanks to its multi-disciplinary nature, MONDRIAN is expected to provide the opportunity to characterize ES-NSCLC from a multi-omic perspective, with a Radiation Oncology-oriented focus. Other than contributing to a mechanistic understanding of the disease, the study will assist the identification of high-risk patients in a largely unexplored clinical setting. Ultimately, this would orient further clinical research efforts on the combination of SBRT and systemic treatments, such as immunotherapy, with the perspective of improving oncological outcomes in this subset of patients.

**Trial registration:**

The study was prospectively registered at clinicaltrials.gov (NCT05974475).

## Introduction

Lung cancer is the leading cause of cancer-related mortality, accounting for more than 257,000 deaths in Europe in 2020 [1]. Non-small cell lung cancer (NSCLC) is the most common type of lung cancer, encompassing diverse histological subtypes. Recent advances in screening initiatives, especially in high-risk populations- have yielded mortality benefits up to 20%: as a consequence, and for the first time, there has been an observed increase in the diagnosis of early-stage disease (ES-NSCLC). This has underscored the imperative to refine the understanding of tumor biology, in order to identify predictive and prognostic to orient clinical management [2].

Currently, those diagnosed with ES-NSCLC are potential candidates for either surgery or radiation therapy (RT) [3]. In the absence of robust evidence from randomized trials comparing the two treatment modalities [4–6], the choice of the optimal treatment is guided by clinical characteristics (such as pulmonary function), equipment availability, and the expertise of individual institutions. In Radiation Oncology, the advent of stereotactic body RT (SBRT) has significantly reshaped treatment paradigms for ES-NSCLC. A relevant aspect of such shift is the utilization of extremely hypofractionated schemes, and the delivery of higher biologically effective doses to the target, whose movements can be tracked in real-time across the respiratory phases. Other than being safe and well-tolerated, SBRT has a specific biological rationale, which consists in counteracting cancer cells repopulation through the induction of vascular damage, immune response, and alterations in the tumor microenvironment [7]. While achieving excellent rates of local control, regional and distant failures remain an issue [8]. Hence, the identification of individuals at higher risk for disease progression holds the potential to reduce progression and disease-related mortality, prevent overtreatment of low-risk patients, reduce avoidable healthcare expenditures and- ultimately- facilitate the transition to fully personalized treatment strategies in this clinical setting. This is especially relevant in the evolving landscape of combined approaches, including- as an example- the SBRT/immunotherapy combination.

Over the past decade, a more profound understanding of NSCLC immunobiology has led to the successful utilization of immune checkpoint inhibitors for locally-advanced and metastatic disease. While safety and efficacy in real-life scenarios are being tested [9, 10], the use of immunotherapy in early-stages has emerged as a hot topic in Thoracic Oncology [11]. Of note, trials are mainly investigating immunotherapy in surgical candidates (e.g. CHECKMATE 816 and KEYNOTE 671 trials), while a specific focus on SBRT is currently lacking [12, 13]. However, considering the well-recognized immunomodulatory effects of SBRT [14], its synergistic integration with immune checkpoint inhibitors holds the promise of enhancing the improvement of the oncological outcomes in poor SBRT responders. Thus, further investigations are mandatory.

To date, knowledge on potential predictors of response to SBRT is limited to a heterogenous set of clinical, radiological, metabolic and dosimetric parameters, stemming mainly from small, retrospective series [15, 16]. Other than these qualitative and semi-quantitative descriptors, the integration of high-throughput information (i.e., “omics”) holds the promise of providing novel predictive features that cannot be inferred from a priori clinical knowledge (e.g. a radiomic signature of radioresistance). Among these -omics approaches, radiomics stands out as the most easily scalable, thanks to both the wide imaging availability and low implementation costs. In contrast, translational approaches- such as genomics- are by far less common. Additionally, the integration of data from different information layers (e.g. radiomics and genomics) could further enhance outcome prediction compared to the use of individual information layers alone [17]. In essence, the rationale behind the integration of multi-dimensional information is that each histopathological, radiological, genomic, transcriptomic feature- whether qualitative, semiquantitative, or purely quantitative, represents the piece of a larger and more intricated jigsaw. Nonetheless, whether the combination of multiple information layers really translates into improved outcome prediction, remains an open question.

## Methods/ design

### Aim and setting of the study

The primary aim of this study- named MONDRIAN (Multi-Omics Integrative Modeling for Stereotactic Body Radiotherapy in Early-stage Non-Small Cell Lung Cancer), is to identify a multi-omic biomarker of response to SBRT in ES-NSCLC. Additionally, the study aims to assess whether the combination of clinical, imaging and biologically-derived information could yield better prediction than individual-omics alone. This will be realized through a data-driven, bottom-up approach integrating prospectively collected data from the radiomic, genomic, and protein domains, to more consolidated clinical parameters, as detailed below.

MONDRIAN is designed as a monocentric, prospective observational explorative cohort trial. It is expected to enroll ES-NSCLC patients treated with either SBRT or surgery with a 1:2 ratio, respectively, for a total of 300 patients, over a 5-year timeframe. The primary endpoint is progression-free survival (PFS) defined as the time between the beginning of SBRT or the date of surgery, and any disease progression (local, regional, distant), death from any cause, or last follow-up, whichever comes first. Secondary endpoints are the investigation of prognostic factors from clinical, imaging, genomic and proteomic data, the longitudinal validation of gene expression and proteomics profiling among tissue- and liquid biopsies-derived samples, and the creation of a permanent dataset of high-quality, prospectively collected multi-dimensional data.

The whole study will be conducted at the European Institute of Oncology (Istituto Europeo di Oncologia, IEO) IRCCS, in Milan, Italy.

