### Power calculations

The main aim of the MONDRIAN study is to assess the predictive value of the multi-omic predictive score for SBRT response, with the primary outcome of interest being PFS. A sample size of 270 allows to verify whether the score (classified as low and high, based on the median value) is able to predict treatment response on PFS with 80% of power [22]. With a median progression-free survival time (MPFST) of 27 and 14 months in the SBRT and surgery groups, respectively [23], for patients with high score, the corresponding hazard ratio (HR) is 0.52. For patients with the low score, we assume a MPFSTs of 14 and 27 months in the SBRT and surgery groups, respectively, with a corresponding HR of 1.93. Under the assumption of uniform distribution for the censoring time during the study period, a two-sided 1% type I error calculation was set to account for multiple testing. Given the possibility of 10% of missing values/lost to follow-up, an approximate number of 300 patients, with a 1:2 ratio for SBRT and surgery, respectively, will be enrolled.

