## Discussion

The rationale of the MONDRIAN study fits into the early stages of applying the omics sciences to Radiation Oncology, and into the wider concepts of personalized medicine. These principles are applied to the largely uninvestigated setting of ES-NSCLC, with the primary aim of investigating factors associated with radiosensitive and radioresistant phenotypes. In addition to seeking a mechanistic understanding of the disease, the study aspires to uncover clinically actionable insights by the identification of different risk profiles for disease progression. Arguably, this would set a benchmark for further investigations on treatment intensification strategies for high-risk patients, which may include dose escalation and/or combination therapies (e.g. immunotherapy).

Several risk mitigation strategies have been developed to ensure sufficient enrollment, accurate prospective collection of reliable data, and- overall- successful study completion. Of these, it is important to underline that interdependence among tasks will be significantly diminished thanks to the training of single- and dual-omics models, in addition to the multi-omic model. This strategy serves two purposes: on the one hand, it minimizes the weight of potentially uninformative data, on the other, it allows to explore how the combination of omic-features contributes to the predictive performance of models.

Another potentially relevant issue may involve negative patient selection in the SBRT cohort. Indeed, SBRT is often regarded as the second-choice curative treatment for ES-NSCLC, particularly in case of contraindications to anesthesia and/or surgery. Consequently, a certain degree of selection bias is anticipated, also due to the non-randomized nature of the MONDRIAN study. Hence, all models will be adjusted using a propensity score, which will be calculated for each patient by combining the beta coefficients of the clinical variables included in a logistic regression model where the treatment (SBRT vs. surgery) serves as the outcome. This adjustment aims to minimize the impact of potential confounders and ensure a reasonable level of comparability between treatment groups. A propensity score approach based on patient matching will also be employed and compared with the method relying on propensity score adjustment.

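### The added-value aim sets a combination that includes clinical data against single omics alone, with no clinical-only reference, so a gain could come from the clinical variables

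*Protocol article*

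**What the plan says.** The protocol article, under Aim and setting of the study, gives an aim beyond finding a biomarker: to assess whether "the combination of clinical, imaging and biologically-derived information could yield better prediction than individual-omics alone". It describes the approach as "integrating prospectively collected data from the radiomic, genomic, and protein domains, to more consolidated clinical parameters", so clinical parameters are part of the integrated model.

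The Discussion says that dependence between the study tasks is reduced "thanks to the training of single- and dual-omics models, in addition to the multi-omic model", and adds that "it allows to explore how the combination of omic-features contributes to the predictive performance of models". It also states that "all models will be adjusted using a propensity score". That score comes from a logistic regression on clinical variables "where the treatment (SBRT vs. surgery) serves as the outcome".

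No section names a model built on clinical variables alone as a comparator. The clinical data for one are collected: Study design describes baseline and follow-up data on general condition, comorbidity, smoking, lung function, blood markers, stage and tumour location.

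**The concern.** A comparison isolates the value of a component only if its two sides differ in that component alone. Here one side has clinical data plus several omic layers, and the other, read literally, has one omic layer and nothing else. If the combination predicts better, there are three candidate explanations: the clinical variables, the additional omic layers, or both. The stated comparison cannot tell them apart.

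Two conclusions are at stake. One is whether integrating omic layers improves prediction, which the Introduction calls unresolved. The other is whether the assays add anything to information that is already collected routinely. PFS counts deaths from any cause, so comorbidity and lung function could plausibly predict it. An analysis plan that followed the aim faithfully would inherit the problem, and a gain due to clinical data could be reported as a gain from multi-omic integration.

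**Working it through.** The plan gives no figure for this aim. Its only calculation, 270 patients raised to about 300 under Power calculations, concerns the score and treatment response. Its arithmetic is consistent (14/27 = 0.52, 27/14 = 1.93, 270/0.9 = 300) but has no bearing here. The check is therefore a reading of the text, with an illustration of size.

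**Step 1. What each stated comparison can isolate.**

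| Comparison | Differs in | Isolates |
|---|---|---|
| Aim: clinical + imaging + biological versus one omic alone | Clinical content and number of layers | Neither |
| Discussion: single- versus dual- versus multi-omic | Number of layers, if clinical content is equal | Integration across omics, on that condition |
| Clinical-only versus clinical + omics | Omic content | Omics over clinical data; not stated anywhere |

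The condition in the second row is not confirmed. The only clinical element stated to be common to all models is the propensity score, whereas the aims section places clinical parameters in the integrated model.

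**Step 2. Can the propensity score stand in for a clinical model?** The score is a sum of clinical variables, each weighted by its coefficient for receiving SBRT rather than surgery. A variable that predicts PFS strongly but hardly affects treatment choice gets a weight near zero. The score therefore summarises who receives SBRT, not who progresses or dies. It is the same in every model, so it does not distort a comparison between them. It does not put the prognostic clinical information into each of them either.

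**Step 3. Illustration of size.** All inputs are assumptions:

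- one standard-normal clinical predictor with hazard ratio 1.3, 1.5 or 2.0 per SD;
- three standard-normal omic variables with no effect;
- exponential PFS with median 20 months at the average clinical value, and uniform censoring over 0 to 60 months;
- Cox models fitted in 300 patients and evaluated in 1,000 new ones, over 60 replicates.

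Mean out-of-sample C-index:

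| Clinical HR per SD | One omic | Three omics | Clinical only | Clinical + three omics |
|---|---|---|---|---|
| 1.3 | 0.501 | 0.498 | 0.573 | 0.564 |
| 1.5 | 0.504 | 0.503 | 0.610 | 0.605 |
| 2.0 | 0.502 | 0.500 | 0.678 | 0.675 |

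Differences from that table, in row order:

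- The aim as worded (clinical + three omics minus one omic): 0.564 − 0.501 = 0.063; 0.605 − 0.504 = 0.101; 0.675 − 0.502 = 0.173.
- Equal clinical content (three omics minus one omic): 0.498 − 0.501 = −0.003; 0.503 − 0.504 = −0.001; 0.500 − 0.502 = −0.002.
- Clinical-only reference (clinical + three omics minus clinical only): 0.564 − 0.573 = −0.009; 0.605 − 0.610 = −0.005; 0.675 − 0.678 = −0.003.

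With useless omics, only the comparison as worded shows a gain.

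**The case against.** A reader might infer that the trial cannot show that omics, or their integration, add anything. The documents do not support that. The Discussion plans single-, dual- and multi-omic models to explore what combining omics contributes, all with the same propensity adjustment. If their clinical content is equal, that sequence answers the integration question, as the second set of differences above shows. The clinical data are also collected, so the trial could test omics against a clinical model.

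A reader might also infer that the observed gain must be inflated, or that it equals a clinical increment plus an omic increment. Neither follows. The article does not give the covariates of each model, and the wording about individual omics could mean one layer as opposed to several, which is how the Introduction frames the question. Increments in predictive performance are not additive either: in the first row of the simulation, adding noise omics to the clinical variable lowered the C-index from 0.573 to 0.564. Eligibility (stage I-II, ECOG 0-1) also narrows two clinical predictors, so the assumed hazard ratios may be too high.

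It can further be said that this is an additional aim of an exploratory study, that the powered question is untouched, that clinical prognostic factors are covered by a secondary endpoint, and that the sequence of models is mentioned only as a safeguard and need not be a full list. A condensed article may leave benchmark models to the full protocol or the analysis plan, and a clinical-only model may be specified there. All this limits the weight of the point. It does not remove it, because the comparison that the article does state is itself badly fixed: it names clinical data on one side only. Performance metric, penalisation and interval method are rightly left to the analysis plan.

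**Conclusion.** The point holds in a limited form. The added-value aim as worded cannot separate the contribution of clinical variables from that of the omics, and no stated comparison tests whether omics add to clinical data. Integration across omics can be addressed by the planned single-, dual- and multi-omic models, on the unstated condition that their clinical content is the same.

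The size for this trial cannot be computed. The 0.06 to 0.17 range shows the mechanism under the assumed hazard ratios and is not a forecast. The conclusion rests on the literal wording of the aim and on the article alone. If the full protocol or analysis plan already names a clinical-only reference and common clinical covariates, only the wording of the aim needs correcting.

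**What to change.** Reword the aim so that a clinical-only model for PFS is the reference, and enter the same clinical covariates in every single-, dual- and multi-omic model. Compare the models on the same patients and the same validation splits, with an interval for each difference in performance:

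- each omic + clinical versus clinical-only, for the value of that omic over clinical data;
- multi-omic + clinical versus the best single-omic + clinical, for the value of integration.

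Keep the propensity score for treatment selection, and state that it does not replace the clinical covariates. The metric and penalisation can be settled in the analysis plan.

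The cost is a change of wording and one extra model. No new data are needed, and Table 1 schedules model building for months 48 to 60. The reported gain from omics may look smaller.

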### Study population

Inclusion criteria are as follows:

Age ≥ 18 years;Histological diagnosis of NSCLC; all histologies will be considered eligible (e.g. squamous, adenocarcinoma, large cell carcinoma);American Joint Committee on Cancer Tumor Node Metastasis (AJCC TNM) classification (8th Edition) clinical stage I-II;Eastern Cooperative Oncology Group (ECOG) performance status 0–1;Ability and willingness to sign a written informed consent for treatment and study participation.No diagnosis of other invasive cancer (within 3 years before the diagnosis of ES-NSCLC);No absolute contraindications to either surgery (e.g. severe comorbidities) or SBRT (e.g. active connective diseases, severe pulmonary fibrosis);No mental diseases or psychiatric disorders that cannot ensure the acquisition of a valid informed consent.

### Study design

The study is divided into five main tasks, summarized in Table 1. Of note, being an observational trial, the care path will strictly adhere to best clinical practice guidelines [3], and no additional examinations will be required with the sole exception of a venous blood sampling, which will be performed at baseline and at the first disease progression or last follow-up (whichever comes first), as an optional part of the study. The aim of this sub-task is to perform a longitudinal validation of gene expression and proteomic profiling between tissue samples and liquid biopsies. Due to the experimental nature of these analyses, along with their potentially high risk/high gain profile- this sub-study is considered as a benchmark, and participation will be limited to 60 patients treated with SBRT. Participation in this sub-study will be optional, and declining will not affect enrollment in the main study.

**Table 1 Tab1:** Summary of the five tasks of the study

Task	Timeframe (months)	Task Description
Task 1- Clinical Study	1–48	Eligibility check and patient enrollment (WP1), collection of baseline patient-, disease- and treatment-related data (WP2), follow-up and collection of patient-, disease and treatment-related data (WP3)
Task 2- Imaging/Radiomic Study	1–60	Collection of qualitative and semi-quantitative CT image metrics (WP4), collection of qualitative and semi-quantitative 18FDG-PET/CT image metrics (WP5), radiomic analysis on CT and [18 F]-FDG-PET/CT images (WP6)
Task 3- Gene Expression Study	1–48	Sample collection and storage of FFPE samples from either the resected tumor or tissue biopsy (WP7), gene expression profiling through the NGS-based assay OIRRA (WP8)
Task 4- Proteomic Study	1–48	Sample collection and storage of FFPE samples from either the resected tumor or tissue biopsy (WP9), proteomics analysis through the PATH-MS method (WP10)
Task 5- Integrative Model Building	48–60	Data cleaning, exploratory data analysis, regularization (WP11), model training and validation (WP12)

**Abbreviations**: [18 F]-FDG-PET/CT: [18 F]Fluorodeoxyglucose positron emission tomography, CT: computed tomography, FFPE: formalin-fixed paraffin-embedded, OIRRA: Oncomine™ Immune Response Research Assay, PATH-MS: (PAThology tissue analysis of Histones by Mass Spectrometry, WP: work package

A detailed overview of the clinical Task 1 is provided in Fig. 1. Specifically, patient-, disease- and treatment-related data will be collected for both cohorts at baseline and during the course of follow-up, as indicated below:

Patient’s characteristics: demographics, performance status, comorbidities (individual and per the Charlson Comorbidity Index), smoking status, pack-years, and body mass index.Patient-reported outcomes questionnaires (e.g. Activities of Daily Living- ADLs- and Instrumental Activities of Daily Living- IADLs- questionnaires).Pulmonary function, assessed by spirometry.Blood-derived inflammation and nutritional markers, including complete blood count and derived parameters (e.g. neutrophil/ lymphocytes ratio), renal and hepatic function, albumin, lactic dehydrogenase.

